## 9. Discussion

This study will allow us to investigate and compare the effectiveness of two different 24-week exercise programs, in different environments, on the levels of the physical fitness, general health, cognitive ability, and quality of life of individuals with IDD. We intend to evaluate a set of quantitative variables at the same time, with the expectation that participants in the intervention groups will show positive changes, taking into consideration previous studies [4,32]. In the control group, no changes in the variables analyzed are expected. It is believed that the expected results can be attributed to the physical and physiological effects of the environment associated with the different exercise protocols proposed, as there is evidence that finds disparate results in PE programs performed in different contexts [66]. The results will be published at the conclusion of the study.

The pilot study that will follow is essential to understand if these two PE programs are effective tools to reduce barriers that hinder/impede their practice [27,28], and their effectiveness in promoting the variables assessed, taking into account the low levels of physical fitness and QoL of this population. Likewise, we intend to contribute with implications for the practice with new interventions with physical exercise, prescription, and effective strategies, which we believe can contribute, at all levels, to individuals with IDD.

The expected physiological benefits are based on the hypothesis that regular PE practice leads to adaptations in both the cardiovascular and musculoskeletal systems that support an overall increase in exercise capacity and performance [66]. It is considered an ideal tool in the prevention and treatment of various types of cardiometabolic diseases, a promoter of physical fitness, performance activities of daily living, and in reducing/mitigating sarcopenia and cognition decline. In addition, neuromuscular mechanisms, namely, the increased expression of neurotrophic factors (i.e., BDNF), the increase in serotonin and norepinephrine, the regulation of the HPA axis activity, and decreased systemic inflammatory signaling [67,68,69,70,71], may be associated with cognitive decline and QoL.

This study has also a multidisciplinary approach, as it is prudent to investigate the combined effects of some independent variables. In addition, we will also examine the hypothetical premise that some objective measures have strong associations with subjective perception measures.

Although there is a clear need to carry out more research on healthy lifestyle interventions for people with more severe levels of IDD (profound IDD), our current intervention is limited to participants with mild to severe IDD, so future studies should take this level of IDD into account

Finally, as with all studies, our study has some limitations, among which we highlight: (1) due to logistical constraints, the groups will not be randomized; (2) it is impossible to control activities outside the PE program, which may affect negatively or positively the variables under study; and (3) the PE program is not adapted to individuals with profound IDD.

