### 2.2. Participants

Adult volunteers, institutionalized in a support institution, located in Leiria, Portugal, recruited by the non-probabilistic convenience method will participate in the program.

In the first step, an individual explanation will be held about the procedures and objectives of the study, as well as the potential benefits, risks, and the time needed for the development of the project.

In a second moment, the participants/family members/tutors will sign a free consent form. Inclusion criteria will be defined: (1) adults with IDD, diagnosed with mild, moderate, or severe IDD; (2) age over 18 years) success in performing movements such as pulling/pushing; (3) capacity to perform the assessments. Exclusion criteria will be defined: (1) individuals who cannot commit themselves for 6 months; (2) individuals with other associated pathologies; (3) contraindications to PE (e.g., high blood pressure); (4) inability to walk unaided; (5) profound IDD; (6) inability to communicate; (7) non-delivery of signed informed consent.

Due to the characteristics of this special population and logistical constraints intrinsic to the development of intervention studies, the sample will consist of the first 21 individuals who agree to participate in the program, aged between 18 and 65. After that, participants will be allocated to one of the three groups. A power analysis (calculated using *G*Power*, version 3.1.9.7 [29] showed that a sample of at least 15 was required to detect a medium effect size (*ES*) of 0.5 (*α* = 0.05, 1 − *β* = 0.95) using a repeated-measures analysis of variance (*ANOVA*), in agreement with some previous studies [30,31]. The effect size of 0.5 was chosen given that this value was verified from studies investigated the effects of exercise on the variables of interest in our study [32,33,34].

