### 4.6. Quality of Life

For the evaluation of QoL in people with IDD, the *Personal Outcomes Scale* [56,57], in the Portuguese version [58] based on the model of Schalock and Verdugo [59], developed at the *Arduin Foundation and Ghent University*, will be applied by technicians with specific training for this purpose.

The Personal Outcomes Scale includes eight domains, each containing five questions, which can be answered through self-report or the report of caregivers, who may be family members or professionals, making a total of forty questions, presented with three response options, through the Likert format, as, for example, often, sometimes, or never, thus making it possible to (1) measure the results of service interventions; (2) reorient public policies to improve these results; (3) improve support management and the service financing mechanism; (4) compare to QoL of citizens; (5) monitoring the application of human and legal rights, provides crucial information so that it can be used to improve the quality of intervention and credible and sustainable practices, important to implement strategies that align at different levels of systems [58].

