## 7. Participation Attendance/Adherence

Individual participation in each PE session will be scored with 0 (zero) if the participant does not attend or 1 (one) if the participant is present at the PE session and participates in it. At the end of the interventions, the participants who do not perform at least 75% of the sessions will be excluded from data processing.

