## 8. Statistical Analysis

In the statistical analysis, descriptive parameters will be used (mean ± standard deviation or percentage) normality and homogeneity will be verified through the *Shapiro*–*Wilk* test and the *Levene* tests, respectively. The existence of significant differences between groups will be analyzed using the *Kruskal*–*Wallis* test and between times using *Wilcoxon* or *Friedman* test. The non-parametric statistic was defined according to the “Central Limit Theorem” [63], in the sense that it will require 30 participants in the sample to have a normal distribution. The magnitudes of the differences will be examined using the *Cohen’s d* effect size [64]. Likewise, associations across studies variables will be verified through the *Spearman* coefficient of bivariate correlations (*r* = 0.10 to 0.29—small; *r* = 0.30 to 0.49—moderate; *r* = 0.50 to 1—strong) [65]. The significance level adopted for all analyses will be *p* < 0.05. For data processing, the computer program *Statistical Package for Social Sciences* (SPSS Science, Chicago, IL, USA), version 28 will be used.

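### The premise of some 'strong' objective–subjective associations rests on a point-estimate label and an open set of pairs, so with at most 21 people chance alone can often supply one

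*Protocol article*

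**What the plan says.** The Discussion (section 9) sets out the premise: "we will also examine the hypothetical premise that some objective measures have strong associations with subjective perception measures". It does not say which pairs are meant, how many would count as some, or at which time point.

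Section 8 gives the method. It says that "associations across studies variables will be verified through the" Spearman coefficient, in bivariate form, and it labels the size of a coefficient as "0.10 to 0.29—small; *r* = 0.30 to 0.49—moderate; *r* = 0.50 to 1—strong". It adds: "The significance level adopted for all analyses will be *p* < 0.05". It states no interval for the coefficients.

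On the subjective side, section 4.6 says: "The Personal Outcomes Scale includes eight domains, each containing five questions". Section 4.7 adds that the scale is applied to the participant and also to a caregiver or reference technician. Section 2.1 has every outcome measured three times.

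On sample size, section 2.2 says "the sample will consist of the first 21 individuals who agree to participate in the program". Section 7 can reduce that number, since "the participants who do not perform at least 75% of the sessions will be excluded from data processing".

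**The concern.** As a description of one coefficient, the size labels are conventional and harmless. The difficulty comes when 'strong' is itself the thing under examination and any of a large number of pairs may supply it.

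- The test attached to each coefficient has a null value of zero, so a small p-value does not show that an association is strong.
- With about 20 people a coefficient has a wide sampling distribution, so values of 0.50 arise by chance at a low but real rate per pair. Over hundreds of pairs that rate adds up.

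At stake is whether the report could present chance correlations as strong links between measured fitness or health and perceived quality of life. The comparisons between groups and over time are not involved.

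**Working it through.** **The plan's own figure.** The only calculation in the document is the sample size of at least 15 for a repeated-measures ANOVA (section 2.2). It is reproduced by the within-subject test with three groups and three times, f = 0.5 and α = 0.05, assuming a correlation of 0.5 between times and sphericity: N = 15, power 0.984. It says nothing about correlations, and no figure is given for them.

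**Inputs.**
- n = 21 at most (section 2.2). The loss through the 75% attendance rule is not given.
- Threshold 0.50, α = 0.05 (section 8). Two-sided testing is assumed.
- Subjective scores: eight domains, or one total score (section 4.6).
- Objective measures: a conservative count over sections 4.1 to 4.5 gives about 33 (anthropometry 4, body composition 1, isokinetic 11, handgrip and ball throw 2, functional tests 3, haemodynamics and oximetry 4, heart rate variability 7, blood 1). I assume 30, with 10 as a narrower reading.
- Correlation among measures within each set: not given, assumed from 0 to 0.7.
- Coefficients of either sign count as strong. The printed label runs from 0.50 to 1, but timed tests score in the reverse direction.

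**One pair, no true association.** From the permutation distribution of Spearman's coefficient at n = 21, P(|r| ≥ 0.50) = 0.022.

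**Does p < 0.05 filter anything?** With t = r·√[(n − 2)/(1 − r²)], r = 0.50 gives t = 0.50 × √(19/0.75) = 2.52 on 19 df, p = 0.021. The critical coefficient is 2.093/√(19 + 2.093²) = 0.433 at n = 21 and 0.497 at n = 16. So for n of 16 or more, every |r| ≥ 0.50 is already significant.

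**Interval around an observed 0.50.** Fisher z = atanh(0.50) = 0.549; SE = √(1.06/18) = 0.243; 0.549 ± 1.96 × 0.243 = 0.074 to 1.025; back-transformed, about 0.07 to 0.77. That runs from below the band labelled small to well inside the band labelled strong.

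**At least one pair among K.** If pairs are independent, P = 1 − (1 − 0.0221)^K:
- K = 3: 0.065
- K = 10: 0.20
- K = 30: 0.49
- K = 240 (30 × 8): 0.995, with 240 × 0.0221 ≈ 5 pairs expected by chance

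Simulation with correlated measures inside each set and no association between the sets (n = 21, one time point) gives:

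| Pairs available | Within-set correlation 0.7 | Within-set correlation 0 |
|---|---|---|
| 30 measures × 8 domains | about 67% | about 99% |
| 30 measures × one total score | about 22% | about 48% |
| 10 measures × one total score | about 13% | about 22% |

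Repeat runs differ by one or two points (65% against 67% in the first cell; the formula gives 20% where the last cell shows 22%).

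**Sensitivity.** At n = 16, an assumed loss of five people, the single-pair chance rises to 0.050, and the 33 × 8 case gives 90–100%. Using all three time points at n = 21 (correlation of 0.7 over time assumed), the 33 × 8 case gives 94–100%.

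**The case against.** The strongest reply is that the document contains no such decision rule. Section 9 promises to examine a premise; section 8 separately lists descriptive labels. Nothing says that one pair at 0.50 settles the matter. This stands: the link is an inference, drawn because no other meaning of 'strong' is offered.

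A second reply is that the size of the problem depends on choices that the document does not make. This also stands. With a total score and few measures, the chance of a false 'strong' pair is well under one half. If only positive coefficients count, the 30 × 8 figure is 94% for independent measures but 33% at a within-set correlation of 0.7, and 30 × 1 gives 29% down to 12%. A reader might infer that the trial will almost certainly report strong associations, or that the question cannot be answered 'no'. The narrower readings do not support either statement.

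Third, a list of pairs is the kind of detail an article may leave to an analysis plan, and the premise is outside the eight hypotheses of section 1. That limits the weight of the point but does not remove it: the labels, the significance level and the use of correlations across the study variables are fixed here, and the article does not mark this analysis as exploratory.

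**Conclusion.** The point holds as a minor one. The fault is the combination of an open set of pairs with a threshold on the estimate; the 0.50 cut-off alone would mislead only about 2% of the time for one pair named in advance. With no true association, the chance of at least one 'strong' pair by luck ranges from about 13% on the narrowest reading considered to about 99% on the widest. The significance rule does not reduce it at n = 21.

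These figures rest on assumed counts of measures, assumed correlations among them, either sign counting, one time point and no loss of participants. They also rest on the inference that the section 8 label is what would decide the section 9 premise.

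**What to change.** In section 8:

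1. Report each Spearman coefficient with its 95% confidence interval beside the size label.
2. Examine the section 9 premise only on a short list of pairs fixed in advance, with respondent and time point stated. An example is the 6-minute walk, sit-to-stand and handgrip, each against the total Personal Outcomes Scale score at baseline, from one named respondent. Three pairs bring the chance of a false 'strong' label to about 6% at n = 21 (1 − 0.95³ = 14% if only 16 people remain).
3. Label all other correlations exploratory and state how many were examined.

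I would not require the lower confidence limit to reach 0.50. At n = 21 that needs an observed coefficient of about 0.77 and would label a true correlation of 0.70 strong only about 21% of the time.

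The change is wording only and needs no new data. The downside is that fewer associations can be claimed from this analysis.

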## 10. Ethics and Dissemination

Any changes to the protocol will be agreed upon by the research team and formally reported to the Faculty of Sport Sciences and Physical Education—University of Coimbra ethics committee prior to application. Written informed consent will be obtained from participants (who will be provided a copy) after the study has been fully explained (i.e., study procedures, objectives, potential risks, and expected outcomes). Each participant will receive a single coded identification number to maintain their confidentiality, and all experimental data will be recorded using these codes.

All data evaluated will be collected and stored strictly for research purposes. The evaluation data will be stored on a laboratory computer, in a folder with a password, to which only the principal investigator will have access and will be kept for a period of 5 years after the end of the investigation. After this period, all data will be irreversibly deleted.

The results of this study will be reported and published regardless of the magnitude or direction of effect, at the intended target of 3 to 6 months after the end date of the intervention (or an earlier date if conditions permit). Communication of the results to the public will begin with study participants, their families, and to the collaborators of the institution. Communication to the scientific community will be carried out through participation in conferences/congresses. Authorship of manuscripts resulting from this research will be based on the following criteria: significant contributions to the conceptualization or design of the research project, formal analysis and/or interpretations of the data, and critical writing and/or review and editing of the manuscript.

## Figures and Tables

**Figure 1 jcm-11-07485-f001:**
[figure not shown]
Timeline for the study design.

**Table 1 jcm-11-07485-t001:** Indoor training program.

Exercise Prescription	Weight Machines		Breathing: Continuous, Not Forced					
	Main Muscle Group/Critical Components		Duration	Speed	Intensity	Rep’s	Series	Volume
“Caterpillar game” or shuttle run	Practitioners dispersed throughout the space, an element is defined to start catching, then, who is caught, joins the colleague forming a “caterpillar” (holding hands) or “back and forth” race, which consists of executing the maximum number of exercises. routes performed at a predetermined distance and cadence.		5 to 7 min					40 min
Treadmill			10 min	Walk	40–80% of HR_max_			
Leg press	Seated; back completely against the bench; feet resting on the press at shoulder width; legs in flexion forming a 90° angle between leg and thigh; the toes in line with knee height. Perform this way the extension of the leg, without any sudden movement—Quadriceps Activation.			Max. concentric eccentric 3 s	40–80% 3RM	8–15	2–3	
Chest press	Seated; back against the bench; arms in pronation, flexed, and elbows in line with the shoulders. Carry out the extension of the same until the level of the chest. Looking forward—Activation of the Big Chest.							
Leg extension	Sitting, completely leaning against the bench; knees bent; ankles positioned on the supports. Perform the extension of the knees, until forming a parallel line between the lower limbs and the ground—Quadricipital Activation							
Lat Pull Down	Sitting in front of the machine; look ahead; slight flexion of the legs, supported on the quadriceps support; grab the handle. Perform the pull-up to the chest area—Latissimus dorsi activation							
Leg curl	Sitting and leaning against the bench; legs in extension; heels positioned on the supports. Perform knee flexion—Activation of the hamstrings							
Shoulder press	Sitting and leaning against the bench; look ahead; hands in pronation, hold the handles. Perform adduction and abduction of the shoulders, or extension and flexion of the upper limbs—Shoulder Activation							
Note: the rest interval between exercises or sets is 30 s.								
Flexibility: dynamic active method (stretching).								
Exercise	Duration (second)	Series	Recovery		Volume			
4 static stretches	30 s	1	Does not exist		2 min			
Note: stretching performed unilaterally, must last 15 s per limb (not in the case of this 1st micro cycle).								

**Table 2 jcm-11-07485-t002:** Outdoor training program.

Exercise Prescription	Resistance Elastic and 1–2 kg Shin Guards		Breathing: Continuous, Not Forced					
	Main Muscle Group/Critical Components		Duration	Speed	Intensity	Rep’s	Series	Volume
“Caterpillar game” or shuttle run	Practitioners dispersed throughout the space, an element is defined to start catching, then, who is caught, joins the colleague forming a “caterpillar” (holding hands) or “back and forth” race, which consists of executing the maximum number of exercises routes performed at a predetermined distance and cadence.		5 to 7 min					40 min
Walk			10 min	March	40% to 80% of the HR_max_			
Stand up/sit down from chair + elastic bands	Sitting, with legs bent, forming a 90° angle between leg and thigh, feet flat on the floor at shoulder width, lift. Perform full trunk extension. The elastic must always be attached under the feet and held with the hands—Quadriceps’s Activation.			Max. concentric eccentric 3 s	6–9 OMNI-RES scale	15	3	
Low row + elastic bands	Seated; arms outstretched in order to grip the elastic. Pull your elbows toward your torso, keeping your back straight and your chest high—Back Activation							
Unilateral knee extension + shin guards	Seated; straight back; knees bent; feet resting on the ground. Carry out the extension of the same, until forming a parallel line between the lower limbs and the ground—Quadricep Activation							
Chest press + elastics	Sitting or standing; arms in pronation, flexed, and elbows in line with the shoulders. Carry out the extension of the same until the level of the chest. Look ahead. The elastic band can be on the dorsal area or on a post/pillar—Activation of the Big Pectoral.							
Single leg curl + shin guards	Standing. Flex your knees until you form a 90° angle between the thigh and the leg—Activation of the hamstrings							
High row + elastic	Standing; upper limbs extended at shoulder level and parallel to the ground; grab the elastic. Flex your upper limbs in order to pull the elastic towards your chest.							
Note: the rest interval between exercises or sets is 30 s.								
Flexibility: dynamic active method (stretching).								
Exercise	Duration (second)	Series	Recovery		Volume			
4 static stretches	30 s	1	Does not exist		2 min			
Note: stretching performed unilaterally, must last 15 s per limb (not in the case of this 1st micro cycle).								

## Data Availability

Not applicable.
